### Concomitant and forbidden drugs

3.2

Participants are not allowed to take drugs that may affect gastrointestinal tract during the study. If necessary, a wash-out period of at least 2 weeks is required before beginning the study. Any participant having received a treatment of Korean medicine to alleviate FD symptoms will be prohibited from participation. However, taking medication for the management of underlying chronic diseases, such as hypertension, diabetes mellitus, and hyperlipidemia, will be allowed. Participants will be instructed to report all the concomitant drugs and treatments conducted before, on every visit.

### Outcome measures

3.3

#### Primary outcome

3.3.1

The total dyspepsia symptoms (TDS) scale is the primary outcome measurement to assess the change of dyspeptic symptoms. If the TDS scores show significant differences between two groups after the administration of NHT (week 4), NHT will be regarded as an effective treatment of FD. The TDS scale is comprised of eight items; postprandial fullness and bloating, early satiety, epigastric pain, epigastric burning, nausea, vomiting, belching, and other symptoms. Each item is based on a 4-point Likert scale, and higher scores are positively correlated with more severe dyspeptic discomforts.^[22]^ TDS will be evaluated at baseline, week 2, week 4, and week 8.

#### Secondary outcomes

3.3.2

1.Overall treatment effect (OTE): To assess OTE, participants will be asked the following question: “How do you feel about the overall treatment effect throughout the past treatment period with respect to your quality of life and dyspeptic symptoms?” The participants will answer based on a 15-point Likert scale ranging from extreme aggravation (−7) to complete relief (+7).^[23]^ OTE will be assessed at week 2, week 4, and week 8.2.Single dyspepsia symptom (SDS) scale: To subordinately assess the severity of dyspeptic symptoms, four aspects of the typical symptoms of FD will be measured based on a 4-point Likert scale; epigastric pain, epigastric burning, postprandial fullness and bloating, and early satiety. Each symptom will be scored in terms of frequency, intensity, and a level of discomfort.^[22]^ SDS will be evaluated at baseline, week 2, and week 4.3.Food retention questionnaire (FRQ): In traditional Korean medicine, food retention is a pathological process that results in symptoms such as abdominal fullness or pain, indigestion, and water brash.^[24]^ FRQ consists of 17 items based on a 7-point Likert scale ranging from disagree very strongly to agree very strongly.^[25]^ The Likert scores of 1, 2, 3, and 4 will be transformed to 0 point, and 5, 6, and 7 to 1 point. If the total score is 6 or more, we will describe the participant as having food retention. FRQ will be measured at baseline, week 2, and week 4.4.*Damum* questionnaire (DQ): DQ is a useful tool for diagnosing a phlegm pattern in traditional Korean medicine, characterized by symptoms such as indigestion, poor appetite, fatigue, and dizziness.^[26]^ DQ consists of 14 items with a 7-point Likert scale ranging from disagree very strongly to agree very strongly. Higher scores suggest higher likeliness of having phlegm.^[27]^ DQ will be measured at baseline, week 2, and week 4.5.FD-related quality of life (FD-QoL) questionnaire: The FD-QoL questionnaire comprises 21 items from four categories; diet, daily activity, emotion, and social functioning.^[28]^ Each item will be evaluated based on a 5-point Likert scale, with higher scores indicating worse quality of life. FD-QoL will be evaluated at baseline, week 2, and week 4. The investigators will be trained thoroughly to ensure all the questionnaires completed accurately and unbiasedly.6.Gastric myoelectrical activity (GMA): GMA will be measured by using a surface multichannel electrogastrography (EGG) (Polygraf ID, Medtronic A/S, Denmark) at baseline and week 4 to detect abnormal gastric motility in PDS or overlap group. The measurement will be performed as described in the previous studies.^[29,30]^ The multichannel EGG consists of three identical amplifiers with a recording range of 1.0 to 12.0 cycles/min. To measure GMA, three pre-gelled active surface electrodes will be applied to pre-abraded skin, corresponding to the corpus (channel 1), the proximal antrum (channel 2), and the distal antrum (channel 3). A reference electrode and a ground electrode will be also attached to abdominal skin. All recordings will be performed in a quiet room and participant will abstain from food intake overnight for at least 6 h. The subject will be kept in a supine position and instructed not to talk, move, or sleep during assessment to avoid interferences that may affect the results. EGG will be performed in three steps. First, a preprandial recording (30 min) will be conducted during the fasting state. Second, the subject will consume 400 mL of a nourishing beverage (New Care; Wellife, Seoul, Republic of Korea). Finally, a postprandial recording (30 min) will be conducted. The EGG dominant frequency and power, percentage of normal/brady/tachygastria and gastric arrhythmia, percentage distribution of EGG power, and post-preprandial power ratio will be analyzed to assess gastric motility. The investigators who operate EGG will receive training before starting the trial to enhance the accuracy of a measurement.7.Standard tool for pattern identification of functional dyspepsia (PIFD): The standard tool for PIFD has been developed after searching for the literature such as Korean and Chinese clinical trials and research articles to confirm the patterns of dyspeptic symptoms. Next, the expert committee assessed the validity of translations and discussed clinical applications of the questionnaire through the Delphi method. This standard tool consists of 40 items including tongue and pulse diagnosis, classifying FD patients into six patterns of identification; pattern/syndrome of(a)deficiency (with cold) of the spleen system,(b)spleen deficiency with *qi* stagnation,(c)disharmony of the liver and stomach systems,(d)tangled cold and heat,(e)dampness-heat encumbering the spleen system, and(f)food retention.

Each weighted value reflects the importance of each symptom. PIFD will be evaluated at screening, and each pattern will be compared with other outcomes.

### Safety assessment

3.4

The following clinical laboratory parameters will be examined to assess the safety of NHT treatment at screening and week 4; white blood cell, red blood cell, hemoglobin, hematocrit, mean corpuscular volume, mean corpuscular hemoglobin, mean corpuscular hemoglobin concentration, mean platelet volume, platelet, aspartate aminotransferase, alanine aminotransferase, gamma-glutamyl transpeptidase, blood urea nitrogen, creatinine, total cholesterol, triglyceride, high density lipoprotein cholesterol, low density lipoprotein cholesterol, glucose, erythrocyte sedimentation rate, and urinalysis. At screening, these laboratory tests and electrocardiography will be executed to decide whether a subject is eligible to enroll before randomization. In addition, adverse events reporting during the study period will be analyzed to verify the safety of NHT in patients with FD.

### Evaluation of compliance

3.5

Treatment compliance will be evaluated every 2 weeks during the period of administration by counting the number of returned containers of NHT or placebo granules. Participants with more than 70% compliance will be included in the per-protocol analysis. All researchers will try to increase the compliance of medications, reminding participants of the study schedule and instructing them to keep taking drugs through frequent phone calls.

### Adverse events reporting

3.6

An adverse event is any unfavorable medical incident experienced by a participant that does not necessarily have a causal correlation with the intervention. All adverse events will be assessed and documented in CRFs at each visit during the entire study period. Proper medical support will be provided to the participant when any adverse event occurs.

A serious adverse event is an adverse event that may result in death, illness requiring hospital admission, life-threatening incident, persistent disability/incapacity, or congenital anomaly/birth defect. The principal investigator will immediately report such cases to the IRB, evaluate and record the time, progress and severity of the events, providing appropriate treatments to minimize and alleviate symptoms. The participants directly affected by the trial will be compensated based on the compensation protocol after consulting the insurance institution.

### Data management

3.7

For the accurate data collection, highly trained investigators and qualified CRCs will use CRFs, which include only random numbers and no subject identifiers to maintain security. The electronic data will be administered in the Mytrial system (http://www.mytrial.co.kr/) at Bethesdasoft Co., Seoul, Korea. User IDs and passwords that allow access to the database will be provided to only authorized personnel. The data management system will be designed to allow electronic data recorded and audited by the automatic editing system (e.g., proofreading of data according to the reference values). The completed CRFs will be locked not to be changed and the data will be analyzed by an independent statistician.

### Quality control

3.8

To maintain accuracy and quality of the study procedure, data monitoring will be conducted by the Unique Marketing & Training Co., a contract research organization located in Seoul, Korea. The authorized clinical research associate (CRA) will confirm the enrollment, blinding, and withdrawal procedures, and CRF completion thoroughly using the standard operating procedures. All the study files, such as informed consent forms and recorded data in CRFs, will regularly reviewed by the monitoring committee. The data monitoring committee has no competing interests.

### Statistical analysis

3.9

The efficacy of NHT will be analyzed on the full analysis set and per-protocol analysis. The last observation carried forward method will replace missing data to assess the robustness in the results. The safety of NHT will be assessed for the participants who are randomly assigned and received the investigational drugs at least once. The outcomes will be handled by an independent statistician.

Statistical analysis will be performed by using the SPSS program, version 20.0 (IBM SPSS Statistics, New York). The data will be expressed as mean ± standard deviation or as numbers with proportions. The changes after taking the investigational drugs will be compared between the experimental group and the control group. A chi-square test or Fisher's exact test will be used for discrete variables, while independent two sample *t* test for continuous variables. Those that do not satisfy normality will be analyzed by the Mann–Whitney *U* test as a nonparametric statistical test. The analysis of variance will be used for subgroup analysis of the changes in each pattern identification. The assessment of long-term therapeutic effects in a certain period from allocation to close-out will be performed on the basis of repeated measures design. The statistical relationship between subjective components of each assessment and objective EGG parameters will be analyzed with regression analysis. For safety assessment, the frequency and severity of adverse events and the changes in laboratory measurements will be compared between two groups. *P*-values <.05 will be regarded as statistically significant.

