### Sample size calculation

2.5

We hypothesize that oral administration of NHT is more effective than that of placebo in relieving FD symptoms. As the first randomized clinical trial of NHT in patients with FD, we referred to a previous study with a modified design using the same primary outcome.^[20]^ The previous study showed 1.4 points of improvement (μ_c_ – μ_t__=_*δ*) in the TDS scores for FD patients after 4 weeks of treatment with a traditional Chinese herb. In this study, the ratio (λ) of the experimental group to the control group will be 1:1, and the sample size was calculated at the 5% significance level (α) and 80% power (1 – β). The formula used to estimate the sample size is as follows, assuming that the standard deviations (SD = σ) of two groups are different and applying the larger variance in common (
[figure not shown]
): 

Considering the dropout rate as 20%, we calculated the necessary sample size to be 116 participants (58 in each group).

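### Last observation carried forward is the only missing-data method stated for a trial that allows for 20% dropout; if it feeds the week-4 TDS comparison it shrinks a true effect, and it adds bias if dropout differs by arm

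*Protocol article*

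**What the plan says.** The Statistical analysis section (3.9) plans efficacy analyses on the full analysis set and per protocol, and compares changes between arms by a two-sample t test, or a Mann–Whitney test if normality fails. Its one statement on missing data is "The last observation carried forward method will replace missing data to assess the robustness in the results". A repeated-measures analysis appears in the same section, but for long-term effects rather than for the week-4 comparison.

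The Primary outcome section (3.3.1) makes a significant between-group difference in TDS at week 4 the criterion for calling NHT effective, and gives the visits: "TDS will be evaluated at baseline, week 2, week 4, and week 8". Only baseline and week 2 precede the endpoint.

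The Sample size calculation (2.5) states "Considering the dropout rate as 20%, we calculated the necessary sample size to be 116 participants". The 20% is one overall figure, not split by arm.

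**The concern.** LOCF treats a participant's score as frozen at the last visit attended. The trial expects TDS to fall over four weeks, so a baseline or week-2 score used for week 4 will on average be too high. Two consequences follow if those values enter the efficacy comparison. A real difference is diluted, because dropouts contribute less than the full week-4 effect. And if one arm loses more participants, that arm looks worse for a reason unrelated to the drug. Twenty per cent of 116 is about 23 participants, enough for this to matter.

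The sentence gives LOCF the purpose of showing robustness. A robustness analysis should vary the missing-data assumption in a controlled direction. LOCF does not do that, so agreement or disagreement with another analysis is hard to interpret.

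**Working it through.** **Inputs from the protocol.** Effect 1.4 TDS points, significance level 5%, power 80%, 1:1 allocation, 20% dropout, 58 per arm (section 2.5); TDS at baseline and weeks 2, 4 and 8 (section 3.3.1).

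**Assumed inputs.** The SD stands in a formula that is not readable in the available text. Two-sided testing, the common improvement, its timing, the dropout timing and the split by arm are also assumptions.

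**Step 1, the plan's own figure.** Per-arm n = 2(1.960 + 0.842)² × SD² / 1.4². With SD = 2.39 this is 15.70 × 5.712 / 1.96 = 45.8, so 46; 46 / 0.8 = 57.5, so 58 per arm and 116 in total. Any SD from 2.371 to 2.396 gives 116. The SD was solved from the answer, so this shows consistency and is not an independent reproduction.

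**Step 2, dilution with equal dropout.** Suppose 20% leave each arm, half before week 2 (baseline carried, change 0) and half after (week-2 score carried), and half of the effect (0.7) is present at week 2.
- Baseline carried forward: 0.80 × 1.4 + 0.10 × 0.7 + 0.10 × 0 = 1.19.
- Only participants with a post-baseline TDS: (0.80 × 1.4 + 0.10 × 0.7) / 0.90 = 1.32.

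Simulation with baseline carried forward (58 per arm, SD 2.39, correlation 0.6, dropout random within arm, common improvement 1 to 4 points) gives estimates of 1.18 to 1.21, power of 66% to 78%, and type I error of 4.6% to 5.6%.

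**Step 3, bias with unequal dropout and no true effect.** Bias = sum over dropout times of (difference in dropout proportion × mean improvement still to come). Take a 3-point improvement in both arms, 1.5 of it by week 2, and half of dropouts leaving before week 2.
- 15%/25%, baseline carried: 0.05 × 3 + 0.05 × 1.5 = 0.225.
- 10%/30%, baseline carried: 0.10 × 3 + 0.10 × 1.5 = 0.45.
- 15%/25%, post-baseline only: (0.125/0.875 − 0.075/0.925) × 1.5 = (0.143 − 0.081) × 1.5 = 0.09.
- 10%/30%, post-baseline only: (0.15/0.85 − 0.05/0.95) × 1.5 = (0.176 − 0.053) × 1.5 = 0.19.

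Simulations of these cases agree:

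| Dropout | Population | Bias (points) | Type I error |
|---|---|---|---|
| 15%/25% | baseline carried | 0.21 to 0.24 | about 7.5% to 9% |
| 15%/25% | post-baseline only | 0.09 | 5.7% |
| 10%/30% | baseline carried | 0.44 to 0.46 | about 16% to 17% |
| 10%/30% | post-baseline only | 0.18 to 0.19 | 6.8% to 7.4% |

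**Step 4, sensitivity to the assumed improvement.** With baseline carried forward and a common improvement of 1 to 4 points, 15%/25% gives bias of 0.07 to 0.30 and type I error of about 5% to 9.5%; 10%/30% gives 0.15 to 0.60 and about 6% to 25%. If every dropout leaves before week 2, 10%/30% with a 2- to 4-point improvement gives 0.4 to 0.8 and 16% to 36%. With a true effect of 1.4, NHT/placebo dropout of 30%/10% gives estimates of 0.48 to 0.94; 10%/30% gives 1.44 to 1.89.

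**Step 5, the alternative.** A likelihood analysis of the observed week-2 and week-4 scores, in the half-before-week-2 scenarios, has null bias of at most about 0.02 points, type I error of 4.3% to 5.3%, estimates of 1.39 to 1.42 for a true 1.4, and power of 79% to 83%. This holds under missing at random.

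**The case against.** The purpose attached to LOCF is the language of a sensitivity analysis. On that reading the primary handling is simply not given in a condensed article and may stand in a full protocol or analysis plan. This stands: a reader might infer that the full-analysis-set result definitely depends on LOCF, but the wording allows either role.

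A reader might also infer that type I error will be inflated. The protocol gives one overall dropout allowance and nothing that predicts imbalance, and with equal non-informative dropout the error rate is nominal. The Withdrawal criteria (2.11) do remove participants who receive prohibited FD treatment, a route that could be related to symptoms, but that is a possibility and not a forecast.

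The larger figures also depend on who is in the full analysis set, which the article does not define. Restricting it to participants with a post-baseline TDS cuts the 10%/30% case from about 17% to about 7%.

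Nor is LOCF strictly stronger than missing at random. The two assumptions are different and not nested; LOCF is the less plausible one here. Finally, the protocol does not say that LOCF feeds the long-term analysis, so a claim that week-8 persistence is assumed is unsupported.

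What remains does not depend on these points: the only stated method is a weak choice in either role.

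**Conclusion.** The point holds conditionally; it should be fixed, with moderate confidence. If LOCF feeds the week-4 comparison, the cost under equal 20% dropout is dilution of a true 1.4 to about 1.2 or 1.3, with the error rate near 5%. Bias and error-rate inflation arise only if dropout differs by arm: under the 3-point assumption, about 0.1 to 0.24 points and 5.5% to 9% for 15%/25%, and about 0.2 to 0.45 points and 7% to 17% for 10%/30%. If LOCF is only a robustness check, the primary test is not necessarily affected, but the check does not test departures from missing at random.

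A reader might conclude that LOCF could by itself create a difference of the size the trial seeks. The figures do not support that: 0.45 is 32% of 1.4, and the most extreme null case, 0.8, is 57%. All these sizes rest on the assumed improvement, timing and dropout splits.

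**What to change.** In the Statistical analysis section, state that week-4 TDS in the full analysis set is analysed by a mixed model for repeated measures with baseline TDS, centre, treatment, visit and treatment-by-visit, the week-4 contrast being primary. Multiple imputation followed by ANCOVA is an acceptable alternative. Assess robustness with a delta-adjusted or reference-based analysis, and report dropout and its reasons by arm. Keep LOCF as a supplementary table at most, and say so.

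The cost is a change of wording and a little programming. The total of 116 stays as it is. The change should be made before unblinding.

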### Randomization and allocation concealment

2.8

For randomization, an independent statistician who is not involved in the clinical aspects of the trial will generate 116 random numbers, using a randomization sequence generator the PROC PLAN of SAS 9.4 (SAS Institute Inc, Cary, NC). A manufacturer will package the investigational drugs identically to conceal the intervention allocation and label with numbers from 1 to 58 for each center (58 in each group and distributed equally to both centers).

Eligible 116 participants will be assigned into either NHT or placebo group with a consecutive random number, according to predetermined allocation list. The statistician will keep random number tables concealed within sealed opaque envelopes until the end of the study.

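### The primary TDS comparison is worded once as week-4 scores and once as changes, both by unadjusted two-sample tests; one baseline-adjusted ANCOVA would reconcile the wording and gain power at no cost

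*Protocol article*

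**What the plan says.** Three parts of the protocol article bear on the primary comparison.

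- **Primary outcome (3.3.1)** gives the decision rule: "If the TDS scores show significant differences between two groups after the administration of NHT (week 4), NHT will be regarded as an effective" treatment. The metric here is the TDS score at week 4. The same section schedules TDS at baseline and at weeks 2, 4 and 8, so a baseline value is collected.
- **Statistical analysis (3.9)** gives the method: "The changes after taking the investigational drugs will be compared between the experimental group and the control group". Continuous variables get an independent two-sample t test, with Mann–Whitney if normality fails. No covariate is named. A repeated-measures analysis is planned, but for longer-term effects, not as the week-4 test.
- **Randomization and allocation concealment (2.8)** says kits will carry a "label with numbers from 1 to 58 for each center (58 in each group and distributed equally to both centers"), so allocation is organised within each of the two centres.

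The Sample size calculation (2.5) does not settle the metric. It says "The previous study showed 1.4 points of improvement" in TDS, expressed as control mean minus treatment mean, and reports "applying the larger variance in common". The readable text does not say whether the difference and the SD refer to week-4 scores or to changes.

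**The concern.** A t test on week-4 scores and a t test on changes from baseline estimate the same treatment effect in a randomised trial, but with different variances. In one dataset they can fall on opposite sides of 5%. Two published sentences that define the primary comparison differently leave open which result counts.

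The second issue is efficiency. The score test does not use baseline TDS. The change test uses it, but with its slope fixed at 1, which is too steep whenever baseline and week 4 have similar spread and are imperfectly correlated. ANCOVA estimates the slope from the data. It also removes the need to choose: with baseline as a covariate, modelling the score or the change gives the same treatment effect.

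**Working it through.** **Inputs from the documents (2.5):** δ = 1.4; 5% significance and 80% power; 1:1 allocation; 20% dropout; 116 in total, 58 per arm.

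**Assumptions:** a two-sided test; 46 evaluable per arm (58 × 0.8 = 46.4); equal SD σ at baseline and week 4; correlation r from 0.3 to 0.7, since the article gives none. The SD stands in a formula that is not readable here, so it is back-solved.

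**Reproducing 116.** With n = 2σ²(1.96 + 0.842)²/δ² per arm, σ = 2.39 gives 2 × 5.712 × 7.85/1.96 ≈ 45.7, rounded up to 46. Then 46/0.8 = 57.5, rounded up to 58 per arm, 116 in total. Any σ from 2.371 to 2.396 does the same. This shows consistency; it does not independently check the plan's SD.

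**SDs of the three analyses, from a score SD σ:**
- week-4 score: σ
- change: σ√(2(1 − r))
- ANCOVA: σ√(1 − r²)

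For 0 ≤ r ≤ 1, 1 − r² is never above 1. It is also never above 2(1 − r), because 1 − r² = (1 − r)(1 + r) and 1 + r ≤ 2. So ANCOVA is at least as precise as both.

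**Power** = Φ(1.4/(SD × √(2/46)) − 1.96), with √(2/46) = 0.2085. Two examples:
- Score test, SD 2.39: 1.4/0.498 = 2.81, so Φ(0.85) = 80%.
- ANCOVA at r = 0.5: SD = 2.39 × √0.75 = 2.07, 1.4/0.4316 = 3.24, so Φ(1.28) = 90%.

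| 2.39 is the SD of | r | Score test | Change test | ANCOVA | Gain over better | Gain over worse |
|---|---|---|---|---|---|---|
| week-4 score | 0.3 | 80% | 66% | 84% | 4 | 18 |
| week-4 score | 0.5 | 80% | 80% | 90% | 10 | 10 |
| week-4 score | 0.7 | 80% | 95% | 98% | 2 | 17 |
| change | 0.3 | 91% | 80% | 94% | 2 | 13 |
| change | 0.5 | 80% | 80% | 90% | 10 | 10 |
| change | 0.7 | 59% | 80% | 86% | 6 | 28 |

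Gains are in percentage points, taken from unrounded powers. A noncentral-t calculation with SD 2.4 gives about one point less (79% for the t test and 89% for ANCOVA at r = 0.5).

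**Disagreement between the two t tests.** This was simulated with normal data, 46 per arm and 2.39 as the score SD (40,000 runs per setting). With a true effect of 1.4, exactly one of the two tests is significant in 27%, 23% and 21% of trials at r = 0.3, 0.5 and 0.7. A separate run with SD 2.40 gave 28%, 23% and 22%. These shares are for the score-SD reading; if 2.39 is the SD of change, the share is smaller at r = 0.3 and larger at r = 0.7.

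**Error rate.** With no true effect, each test alone rejects in about 5% of trials. Taking whichever is significant rejects in 8.4%, 9.0% and 9.5%.

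**Centre.** If centre explained 2%, 5% or 10% of the variance (assumed), adjusting for it would lift power from 80% to about 81%, 82% or 84%.

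**The case against.** The strongest reply is that the two sections can be read together. Section 3.3.1 introduces TDS as a gauge of how symptoms change, so it may fix the instrument and time point, while 3.9 supplies the metric for all outcomes. That reading is possible, but the decision sentence in 3.3.1 still says scores, so a clarification is needed. A statistical analysis plan may already choose one version; it would still differ from one of these two sentences.

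The rest of the reply stands in large part. An unadjusted t test is valid in a randomised trial, the sample size appears to have been built for such a test, and the size of the gain depends on an SD and a correlation that cannot be read from the article.

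Several stronger readings are tempting, and the document does not support them:

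- **That the plan ignores baseline.** This is true only of the score version; the change version subtracts it.
- **That the trial's error rate is about 9%.** This needs the version to be chosen after the results are seen. The article does not plan that, and it assigns the analysis to an independent statistician. The switch to Mann–Whitney is tied to non-normality, so it is not a free choice either.
- **That a result favouring placebo would count as success.** The decision sentence names no direction, but section 2.5 hypothesises that NHT beats placebo and defines the difference as control minus treatment.
- **That the analysis sets are left unranked.** The article says "The efficacy of NHT will be analyzed on the full analysis set and per-protocol analysis". Which of the two is primary is detail that an article may leave to the full protocol or analysis plan.
- **That omitting centre biases the result.** It is at most mildly conservative and costs little.

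**Conclusion.** The point holds as a discrepancy in wording together with an avoidable loss of power. It does not show that the planned test is invalid. Sections 3.3.1 and 3.9 describe two different unadjusted tests, which would disagree in roughly 21–28% of trials if the effect is 1.4, the week-4 SD about 2.4, 46 per arm are evaluable and r lies between 0.3 and 0.7. The 80% target in 2.5 is secured only for the version to which the plan's SD belongs; the other version could have as little as 59% power or as much as 95% over that range.

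ANCOVA gains about 10 points at r = 0.5. At r = 0.3 or 0.7 it gains about 2–6 points over the better version, and it gains up to about 28 over the worse. That ANCOVA is at least as precise as both follows from the variance formulas for any r between 0 and 1, given equal SDs; the size of the gain rests on the assumed SD and correlation.

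**What to change.** In 3.3.1 and 3.9, name the same single primary analysis: ANCOVA of week-4 TDS on treatment, baseline TDS and centre, reporting the adjusted mean difference with its 95% CI. Centre belongs in the model because kits are allocated within centre, though its gain is small. Word the decision rule in 3.3.1 in terms of that adjusted difference, and fix it before unblinding.

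Use the same baseline-adjusted model for the continuous secondary outcomes that have a baseline: SDS, DQ, FD-QoL and the EGG measures. It cannot be used for OTE, which is first asked at week 2; the unadjusted comparison can stay there.

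The cost is a change of wording. Baseline TDS and centre are already recorded, the model can be fitted in the planned SPSS version, and no participants, visits or measurements are added. The planned 116 can stay.

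### A normality check on the outcome data decides whether primary week-4 TDS is tested by a t test or by Mann–Whitney, so the efficacy verdict may not address the mean difference for which the trial was sized

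*Protocol article*

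**What the plan says.** All references are to the protocol article.

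- **Success rule (3.3.1, Primary outcome).** "If the TDS scores show significant differences between two groups after the administration of NHT (week 4), NHT will be regarded as an effective treatment". No test is named there. TDS has eight items: "Each item is based on a 4-point Likert scale, and higher scores are positively correlated with more severe dyspeptic discomforts". It is measured at baseline and at weeks 2, 4 and 8.
- **Test (3.9, Statistical analysis).** "The changes after taking the investigational drugs will be compared between the experimental group and the control group". A chi-square or Fisher's exact test "will be used for discrete variables, while independent two sample" t test is the default for continuous variables. Then: "Those that do not satisfy normality will be analyzed by the" Mann–Whitney U test. The rule covers every continuous outcome. The repeated-measures analysis in the same section is for long-term effects, so it does not replace the week-4 test.
- **Reporting (3.9).** "The data will be expressed as mean ± standard deviation or as numbers with proportions".
- **Analysis sets (3.9).** Efficacy is analysed in both the full analysis set and the per-protocol set.
- **Sizing (2.5, Sample size calculation).** "The previous study showed 1.4 points of improvement", defined as a difference of two means (μc − μt = δ); "the sample size was calculated at the 5% significance level" and 80% power, with 20% dropout, giving 58 per group.

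**The concern.** The t test and Mann–Whitney answer different questions. The t test addresses the difference in means, which is what section 2.5 sized and what section 3.9 will tabulate. Mann–Whitney addresses whether a value from one arm tends to exceed a value from the other. The two coincide for a pure shift in location but not in general. Under the stated rule, a feature of the outcome data settles which question the primary P-value answers.

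Three things are at stake:

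- The P-value that declares NHT effective and the means reported beside it may refer to different hypotheses.
- The full-analysis and per-protocol sets could fall on opposite sides of the check, so their comparison as a test of robustness would mix two hypotheses.
- Both branches are unadjusted two-group comparisons. The comparison of changes subtracts baseline TDS but neither branch adjusts for it, although it is collected on everyone.

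**Working it through.** **1. The plan's own sample size.** The formula and its SD are in an image that is not shown, so N cannot be reproduced independently. Back-solving with n = 2(z₀.₉₇₅ + z₀.₈₀)²·SD²/δ², δ = 1.4 and division by 0.8 for dropout:

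- SD 2.39: 2 × (1.960 + 0.842)² × 2.39² / 1.4² = 45.7, so 46 evaluable per arm; 46/0.8 = 57.5, so 58. This matches the stated 58 per group.
- SDs that return 58: 2.371–2.396 (two-sided, division by 0.8); 2.423–2.448 (two-sided, multiplication by 1.2); 2.671–2.700 (one-sided, division by 0.8).

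I take 46 evaluable per arm and SD about 2.4, as assumptions. The mean comparison then has power Φ(1.4/(2.39·√(2/46)) − 1.96) = Φ(0.849) = 80.2%.

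**2. How often the rule switches, and what that costs.** Assumptions: integer scores with range 0–24, baseline SD 2.4, baseline correlation r = 0.5, 46 per arm, and Shapiro–Wilk at 5% in each arm as the normality check (the article names none). About 36% of trials with rounded-normal scores go to Mann–Whitney, and type I error of the two-stage rule is 4.8%. Power at a true difference of 1.4:

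| Assumed scores | t test | Two-stage rule | Baseline-adjusted model |
|---|---|---|---|
| Rounded normal | 78.4% | 77.7% | 88.1% |
| 40% responders | 67.5% | 65.6% | 77.7% |

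The cost of the switch is the t test minus the two-stage rule: 78.4 − 77.7 = 0.7 points and 67.5 − 65.6 = 1.9 points. The gain from adjustment is the adjusted model minus the t test: 88.1 − 78.4 = 9.7 points and 77.7 − 67.5 = 10.2 points.

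**3. Other shapes.** Integer change scores, 46 per arm, same check, 5,000 runs each. SD is 2.39 except in the last row, where controls and non-responders have SD 1.9.

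| Assumed shape | Switches | Two-stage rejects | t test rejects |
|---|---|---|---|
| Same skew (gamma, shape 2), no difference | 100% | 4.8% | 4.8% |
| Same skew, shift of 1.4 | about 100% | 89.2% | 78.5% |
| Opposite skew, equal means | 100% | 19.1% | 5.5% |
| Mean difference 1.4 from 25% responders (0.25 × 5.6) | 80.9% | 56.1% | 75.1% |

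Across all the change-score scenarios, including rounded-normal ones, the two tests disagree on significance in 2–22% of trials.

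**4. Where the 10 points come from.** With equal variances at both visits, the change score has variance 2σ²(1 − r), which equals σ² at r = 0.5. The baseline-adjusted residual variance is σ²(1 − r²) = 0.75σ². So the SD falls from 2.4 to 2.4 × √0.75 = 2.078, and power rises from Φ(2.798 − 1.96) = 79.9% to Φ(3.230 − 1.96) = 89.8%, in line with the simulation.

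The article gives no r, so a range is needed. Taking r = 0.3, 0.5 and 0.7, adjusted power is 83.5%, 89.8% and 97.5% if 2.4 is the SD of the week-4 score (factor 1 − r²). It is 93.4%, 89.8% and 85.9% if 2.4 is the SD of the change (factor (1 + r)/2). Each compares with 79.9% for an unadjusted test of that same quantity.

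**The case against.** The fallback is written down in advance, it is a common convention, and an independent statistician applies it after the CRFs are locked. That largely answers any suggestion of analyst discretion. The article is a condensed document, so the exact normality criterion may sit in a fuller plan, and its absence is not the point here. Group means will be reported whichever test supplies the P-value. All of this stands. It leaves the narrower point that the article affirmatively makes the primary hypothesis depend on the data.

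Some stronger readings are tempting but not supported:

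- **That the rule inflates false positives.** With the same distribution in both arms, type I error is 4.8%. The 19.1% needs opposite skew with equal means, an assumed shape that nothing in the article suggests.
- **That dropping the pre-test recovers about 10 points of power.** Nearly all of that gap is baseline adjustment. Fixing the plan's own t test would recover only 1–2 points in those scenarios.
- **That ties in a summed integer scale force the rank test.** About two thirds of simulated rounded-normal trials pass the check.
- **That the switch is what prevents adjustment.** The default t test does not adjust either, and rank tests can be stratified by centre.
- **That the rule always loses power.** With a skewed pure shift it gains (89.2% against 78.5%).

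**Conclusion.** The point holds as a question of what the primary analysis estimates, not as an error-rate defect. As stated, section 3.9 leaves open until the data are seen whether week-4 TDS is judged on the mean difference behind the sample size or on a rank comparison, and it allows the two analysis sets to differ.

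Under near-normal or 40%-responder assumptions the switch costs about 1–2 points of power. Under other shapes the effect can be large in either direction, from about +11 points (89.2 − 78.5) to −19 points (56.1 − 75.1). The separate gain available from baseline adjustment is about 10 points at r = 0.5.

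Every simulated figure rests on an assumed SD, correlation, score distribution and normality test, because the article shows none of them. It is worth correcting because the change is nearly free and settles what the verdict means. An analysis plan that is not shown may already have fixed the test; if so, the article's rule should be brought into line with it.

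**What to change.** For TDS, delete the normality switch in section 3.9 and name one primary analysis in advance: a linear model of week-4 TDS on treatment, baseline TDS and centre, whatever the distribution, reporting the adjusted mean difference with its 95% CI. Use the same model in the full-analysis and per-protocol sets. Keep a rank test as a named sensitivity analysis, stratified by centre if wished.

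HC3 or bootstrap intervals, and a log transformation fixed in advance for EGG power, are optional refinements.

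The cost is wording only. Baseline TDS and centre are already recorded. At the assumed SD of 2.39, 46 evaluable per arm already give 80.2% power without adjustment, so N = 116 need not change.
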